## Methods

### The design and key features of implementation and evaluation

We employ implementation-effectiveness hybrid study using mixed-methods [26]. This includes quasi-experimental design for quantitative assessment of SBIR implementation (adoption/coverage of intervention) and effectiveness (patient behaviour change and health service use) outcomes. We use both quantitative and qualitative methods to evaluate the implementation processes and providers’ experience of integrating SBIR into their workflows and patients’ experience of the SBIR intervention and of health behaviour change. Each participating site participates in a 6-month pre-implementation period, followed by 15-month SBIR implementation research period. Patients are followed up at 1, 6, and 12 months after they receive the SBIR intervention (Figure 2). Clinical sites that had used Connect Care for at least 6 months prior to recruitment into this project, and where the team identified health promotion and disease prevention as a priority, and expressed interest in participating in the study were engaged to participate.

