**Figure 2 F2:**
[figure not shown]
Overview of Intervention Implementation Design.

During the 6-month pre-implementation period, our onsite research coordinators recruit a no-intervention (control/comparison) group of study participants and conduct risk factor screening on recruited patients using paper-based version of the same screening tools as those in Connect Care that will be used during SBIR implementation. These patients do not receive risk factor screening by clinical team members and are not offered brief intervention and referrals. The 15-month SBIR implementation serves as the intervention period of the study during which patients are recruited to participate in the intervention group. Note that all patients served by the participating clinics/units during the intervention period are *eligible* to receive the SBIR intervention, regardless of whether or not they agree to participate in the research study. Over the course of the 15 months intervention period, as the SBIR practice is increasingly embedded into routine care, we expect a growing proportion of the patients served by the participating clinical teams will receive SBIR. Enrolled research participants are followed up over the course of 12 months (1, only for intervention group, 6, and 12 months) for collection of behaviour change and health services utilization data. During the monitoring of participant recruitment, any control participants who had subsequent visits to intervention sites and received the intervention at that time were excluded from the study.

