## Research plans for evaluation of intervention effectiveness outcomes

*Study design and participants:* We use a quasi-experimental study design (pre-post with a comparison group). The intervention group are patients from participating units during the SBIR implementation period who screen at increased risk on any of the three risk factors and received brief intervention and referral support. The comparison group are patients from the same units, during a 6-month pre-implementation period, identified as having increased risk on any of the three risk factors, but who do not receive the SBIR intervention.

Study inclusion criteria for the target patient population to be enrolled in the effectiveness study include: Adult patients (>18 years) who are residents of Alberta, have the ability to engage in the SBIR process and data collection, and are attending the participating sites during the study period. Research assistants enroll the eligible patients in the study after they provide informed consent. The patients with severe disease conditions (i.e., unconsciousness and end-stage care) or those with mental or cognitive incapacity are excluded.

*Outcome definition and measurement for both groups:* Key outcomes are patient behaviour change in relation to the modifiable risk factors and health care utilizations in the year after recruitment to the study. Measurement of patient’s behaviour changes involves: questions on patients’ intention to change behaviour, their uptake of referral services (for those who received referrals), and changes in risk level as measured using the same risk factor screening tools used during the SBIR intervention. We also ask patients about tobacco use reduction, tobacco quit attempts, seven- and 30-day tobacco abstinence. The data are being collected via telephone interviews at 6 months follow-up after the index clinic visit, or discharge from a hospital stay, during which the patient was recruited into the study. A sample of participating patients are also called at 1 month after their hospital/clinic visit to ask them about their experience of the SBIR intervention.

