Health care utilization measures include hospital readmissions and emergency visits within one year of the index discharge/visits. These outcomes are of particular importance to facilitate outcome comparisons with other studies as well as because they are important to provide cost-effectiveness assessments to support intervention spread/scale decisions by health system administrators. The health care utilization data will be obtained from linked administrative health databases accessed through the Department of Data and Analytics, the custodian of these routinely collected healthcare data (Table 1).

Data on potential confounding variables including sociodemographic and socioeconomic status for both groups are collected during the 6 months patient follow-up interviews. Diagnosis and comorbidity related variables will be obtained from the administrative health databases. A detailed data collection plan is shown in data collection matrix (Table 1).

*Sample size:* SBIR intervention can increase smoking quit rate at 6-months by 11% [40], reduce alcohol misuse rate at 5-months by 19% [41], and increase patients’ average daily physical activity level by 22% [42]. Based on sample size estimation in relation to tobacco use (with effect size of 11%), we will need a maximum of 1,000 patients in each group (a total sample of 2,000 for controlled and intervention groups) to detect the smallest difference, among all outcomes, between the groups (with a study power of 80% and alpha of 0.05). This is the maximum number needed since tobacco is the least prevalent condition and it will also have the smallest proportion of change in behaviour after intervention, among the three risk factors. We will recruit a total sample of 4,000 (2,000 sample for controlled group and 2,000 for intervention group) to account for the anticipated 50% loss to follow up or nonresponse rate. The expected dropout rate is determined based on our previous paper-based SBIR pilot study [22].

*Analysis:* We will use log-binomial regression models to estimate risk difference and relative risk (for health behaviour change outcomes), and Cox proportional competing risk regression models to estimate hazard rate difference and hazard ratio (for health care use outcomes), to compare outcomes between the two groups adjusting for confounders, such as reasons or diagnosis for visits/admissions, comorbidity, and socioeconomic status.

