Cost-effectiveness analysis will document the economic value of the SBIR intervention in order to communicate that value to decision-makers. Cost reduction/avoidance within one year, attributable to SBIR, will be estimated based on the reduction in 1-year readmissions and emergency visits, compared to the non-intervention comparison group. Estimates of this economic impact will be provided by applying hospitalization and emergency visit cost data, provided by Canadian Institute of Health Information (CIHI), to the utilization estimates from the above-mentioned models. Intervention implementation cost data are being collected throughout the project.

*Ethical considerations:* This study has received ethics approval from the Health Research Ethics Board of Alberta – Community Health Committee- at the University of Calgary (HREBA.CHC-22-0058).

*Involvement of people with lived experience:* IPiC-Health project has 7 patient advisors, who closely work with the research and innovation team of IPiC-Health project. The patient advisors provide insights based on lived experience to inform SBIR pathways, the research and implementation plan, development of resources, brief conversation scripts, and provide advice on acceptability and appropriateness on all aspects of the research and intervention. The Patients advisors consist of individuals connected to the Alberta Strategy for Patient Oriented Research SUPPORT Unit (AbSPORU) and Patient and Community Engagement Research (PaCER) | University of Calgary-trained patient researchers who have lived experience of care in Alberta’s patient care settings and/or with the risk factors targeted by the SBIR intervention.

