## Expected Results and Applicability

Thus far 4 inpatient units and 4 ambulatory clinics in Calgary and Edmonton cities in Alberta have participated in this project. Among those, 1 inpatient unit and 4 ambulatory clinics have completed the 6 months control period and started the implementation of SBIR, and remaining units/clinics are in the 6 months control phase. We have recruited a total of 2015 patients as control research participants (i.e., medium or high-risk level on any of the three risk factors). Of those, 1000 have completed 6 months follow-up calls. A total of 447 patients have received SBIR support from the participating units/clinics, with 175 patients being intervention research participants (i.e., consented for follow up survey). Among those intervention research participants, 48 have completed 1 month follow up survey calls, 75 have completed 6 months follow up calls, and 23 have participated in in-depth qualitative interviews. Approximately 50% of patients are responding to follow-up efforts.

The research participants recruitment and data collection activities are undergoing and key learnings to date are as follows.

High screening uptake: Providers are consistently screening and documenting for the risk factors.Low brief intervention rates: Offering brief advice or engaging patients in conversations about behavior change remains relatively low.Low documentation of brief intervention: When brief interventions are provided, they are often not documented in the Connect Care system.Referral gaps: Referral pathways—particularly for physical activity and alcohol use—are unclear, and referral functionalities for these risk factors are not currently integrated into the Connect Care system.Facilitators of implementation: Implementation is supported by clinical champions, embedded project staff at implementation sites, and ongoing rapid assessment and feedback.Participant eligibility challenges: Many patients are ineligible for the intervention or study participation due to critical health conditions particularly in some high acute care settings. This indicates that careful consideration of the setting and patient acute is important when deciding whether to implement SBIR.Improved recruitment: Using both in-person and phone-call recruitment strategies has led to an increase in participant numbers.

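### Excluding controls who return and receive SBIR removes utilization events from the control group only, and tilts the readmission, emergency-visit and cost comparison against SBIR by an unknown amount

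*Protocol article*

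**What the plan says.** The exclusion is in Methods, under the design and key features of implementation and evaluation, in the text after Figure 2: "any control participants who had subsequent visits to intervention sites and received the intervention at that time were excluded from the study". It is in the past tense, so it has evidently already been applied. The sentence opens by placing the rule within the monitoring of recruitment and does not say how long the rule runs. No equivalent is stated for intervention participants.

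The calendar is fixed in the same section: "Each participating site participates in a 6-month pre-implementation period, followed by 15-month SBIR implementation research period". The effectiveness section draws controls from the same place: "The comparison group are patients from the same units, during a 6-month pre-implementation period". Once implementation starts, all patients of the unit are eligible for SBIR, and "we expect a growing proportion of the patients served by the participating clinical teams will receive SBIR".

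On outcomes, "Health care utilization measures include hospital readmissions and emergency visits within one year of the index discharge/visits". These are analysed with "Cox proportional competing risk regression models to estimate hazard rate difference and hazard ratio (for health care use outcomes"), adjusted for diagnosis, comorbidity and socioeconomic status. Cost avoidance "will be estimated based on the reduction in 1-year readmissions and emergency visits, compared to the non-intervention comparison group".

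**The concern.** Whether a control stays in the study depends on something that happens during that person's follow-up. At an inpatient unit, a return at which SBIR is delivered is a readmission, so the rule deletes both the event and the patient. At a clinic, a return is not itself the outcome, but sicker patients plausibly come back more often. Intervention participants who return are, as far as the text goes, retained with their events.

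The control event rate therefore falls for a reason unrelated to SBIR. Adjusting for baseline characteristics cannot put deleted events back. The cost estimate intended for decision-makers uses the same contrast and inherits the error. The distortion would also grow as implementation succeeds, since more returning controls would then receive SBIR.

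**Working it through.** **The plan's own figures.** The article gives no number of excluded controls, no return rate, no delivery rate and no expected readmission risk, so there is no stated figure to reproduce for this point. The one figure borrowed below is the recruitment target, which checks: 1,000 / (1 − 0.50) = 2,000 per group.

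**Step 1: how long the rule can act.** Let a control be enrolled x months into the unit's control period, 0 ≤ x ≤ 6. SBIR runs from month 6 to month 21.
- Utilization: follow-up ends at x + 12, at most month 18. Overlap with SBIR = (x + 12) − 6 = x + 6, that is 6 to 12 months. With uniform recruitment the mean is 9 of 12 (75%).
- Six-month behaviour interview: overlap = (x + 6) − 6 = x, that is 0 to 6 months, mean 3.

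This is calendar overlap, not a return rate.

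**Step 2: direction.** Let R be the true one-year risk in both groups (no SBIR effect), q the share of controls with an event who are removed, and s the share without an event who are removed. The observed control risk is

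Rc = R(1 − q) / [R(1 − q) + (1 − R)(1 − s)].

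With R = 30% (assumed):

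| q | s | Rc | R/Rc | Chance of a significant false result against SBIR* |
|---|---|---|---|---|
| 10% | 0% | 0.270/0.970 = 27.8% | 1.08 | 32% |
| 20% | 0% | 0.240/0.940 = 25.5% | 1.18 | 87% |
| 20% | 10% | 0.240/0.870 = 27.6% | 1.09 | 37% |
| 20% | 20% | 0.240/0.800 = 30.0% | 1.00 | none beyond alpha |

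*2,000 recruited per group less the removed controls; two-sided alpha 0.05 assumed.

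The bias vanishes when q = s and runs against SBIR when q > s.

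**Step 3: plausible size.** Simulation with no SBIR effect. Assumptions: 0.6 acute events per patient-year, gamma heterogeneity with variance 1, the Step 1 overlap, a share a of acute contacts at a participating unit, and probability c that such a contact delivers SBIR. Expected triggering contacts per control = 0.6 × 9/12 × a × c = 0.45ac.

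| a and c | 0.45ac | Hazard ratio when the truth is 1.00 |
|---|---|---|
| 10–20% each | 0.0045 to 0.018 | about 1.01 to 1.04 |
| 30–50% each | 0.041 to 0.113 | about 1.09 to 1.29 |

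In the second row about 4–10% of controls are deleted (slightly below 0.45ac at the top because some people have more than one triggering contact).

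In related runs where returns were purely scheduled clinic visits unrelated to acute use, the risk ratio stayed at about 1.00. No scenario favoured SBIR.

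**Step 4: a rough ceiling to date.** Expected Results and Applicability reports 447 patients given SBIR, 175 of them intervention participants, leaving 447 − 175 = 272. At an assumed 30% risk, 2,015 × 0.30 ≈ 604 controls would have an event. Deleting half of them (302) would exceed all 272; deleting a quarter (151) would require 151/272 = 56% of the 272 to be former controls. Very heavy deletion had therefore not happened by that report, though roll-out continues.

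**The case against.** The rule has a legitimate aim: the effectiveness section defines controls as people who do not receive SBIR, and retaining contaminated controls dilutes the contrast. Analysis detail such as censoring may sit in a statistical analysis plan that is not shown. That does not remove the point, because the article itself fixes who leaves the study and on what trigger.

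Several stronger readings are tempting but unsupported:
- A reader might infer that only controls who never came back remain, or that frequent returners as a class are removed. Exclusion requires a return and receipt of SBIR; returners who receive none stay in with their events. The article reports that "Offering brief advice or engaging patients in conversations about behavior change remains relatively low".
- A reader might infer from the 9-month overlap that such returns are routine. No return rate is given. Of the five units that had started SBIR, four were ambulatory clinics and one was inpatient, so the identity of return and readmission applied to one live unit.
- A reader might assume that the rule runs through all 12 months. The reference to recruitment monitoring leaves that open.
- A reader might extend the bias to the behaviour outcome. The overlap there averages 3 months and no direction is established.
- A reader might take it as stated that returning intervention participants are kept. That is the natural reading of the text's silence, not an explicit provision.

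These points limit size and scope. They do not alter the fact that the rule is stated for one group only and is triggered by an event tied to the outcome.

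**Conclusion.** The point holds for utilization and cost. As written, the exclusion lowers control readmissions and emergency visits and biases the comparison against SBIR, or leaves it unchanged if returns are unrelated to acute use. The direction follows from the rule for inpatient returns; for clinic returns it needs a positive link with acute use, which is plausible but not documented.

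The size cannot be established from the article. The Step 3 ranges rest on assumed event, return and delivery rates and on the rule operating throughout follow-up. Given the reported low delivery, the lower range may be nearer the present position. The conclusion concerns this exclusion alone, not the net of all biases in a before-and-after comparison, and it does not show that SBIR will appear ineffective or harmful.

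**What to change.** Replace the exclusion before analysis:

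1. Keep every enrolled control in the group of enrolment for the utilization and cost analyses, and record the date of any later SBIR receipt.
2. In the main analysis, count all 12 months regardless of later SBIR.
3. Add a sensitivity analysis that censors controls after the triggering visit, with that visit counted where it qualifies as an outcome. In a time-to-first-event model a qualifying readmission precedes the SBIR delivered during it, so the event is preserved.
4. Restore controls already excluded, using administrative data where consent allows. Treat missing six-month interview covariates as missing data.
5. Report how many controls were excluded and when, and state the period over which the rule was applied.

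The cost is modest: utilization comes from administrative databases, and the article says analysis awaits complete data. There are two downsides. Contaminated controls dilute the contrast somewhat, by an amount not calculated here. Controls excluded before the six-month interview may also lack the sociodemographic and socioeconomic covariates collected there.

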### Research plans for evaluating implementation outcomes and process

*Study design and participants:* We use a quasi-experimental interrupted time-series design, covering a 6-month pre-implementation period and the last 12 months of the 15-month SBIR implementation period. The first three months of the implementation period are not used in analysis because we expect the quality of the SBIR intervention will mature over the first few months during which the clinical team learn to apply the practice.

*Definition and measurement of implementation outcomes*: Intervention reach (number) and patient population coverage (proportion) will be measured for each component of the SBIR intervention. Thus, the number of patients i) screened; ii) advised; and iii) referred in relation to each risk factor will be extracted each month from the Connect Care data. The denominator for the coverage (proportion) measures will be based on the total number of patients seen by a participating unit in the same month.

*Analysis:* For each outcome, we will calculate monthly summaries, aggregated across participating units. A Poisson regression model will be used to estimate the difference between the post-intervention observed rate and the “spontaneous” rate that would have occurred had SBIR been not implemented. The analysis will account for seasonality by decomposing the data in trend, seasonal, and random components, and then removing the seasonal component.

*Implementation process evaluation:* We employ qualitative and quantitative methods using surveys, focus group discussions, and in-depth interviews to understand the SBIR implementation process and patients’ and providers’ experience. This involves assessments of: factors affecting providers’ implementation/adherence to SBIR; providers’ perceptions of SBIR acceptability, appropriateness, and feasibility; providers’ perceptions of their role in patient-centered, preventive care; patients’ experience (acceptability, perceived stigma, and challenges with SBIR and behaviour change). We are using the Consolidated Framework for Implementation Research (CFIR) and Theoretical Domains Framework (TDF) to guide the ongoing assessment of implementation and obtain a comprehensive understanding of barriers/facilitators, behavior/practice change of healthcare providers, and the contextual factors that influence SBIR implementation [37,38,39]. A detailed data collection plan for both implementation and effectiveness outcomes are shown in data collection matrix table (Table 1).

**Table 1 T1:** Data Matrix.

OUTCOME CATEGORY	OUTCOMES	MEASURES	DATA SOURCES	DATA COLLECTION METHODS

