### Anticipated implementation challenges and strategies employed

Based on lessons learned from our previous SBIR pilots and our review of the global literature, we anticipated several factors that can hinder or help the implementation of SBIR in hospitals. These include: change fatigue and competing priorities, patients’ perceived or experienced stigma and providers’ discomfort to discuss behavioural risk factors with patients, functionality of the Connect Care system to support this work, limited capacity/motivation to provide preventive care in hospital settings, resources/support available to deliver SBIR or Connect Care support, and the adaptability of SBIR within a variety of clinical workflows [22,23,34,35]. Accordingly, several strategies (tools, training, technical assistance, and quality improvement methods) are planned and implemented together with stakeholders at each participating site to address the anticipated barriers and facilitate successful SBIR implementation and adaption [35,36]. The tools include a SBIR implementation guide, a single page information sheet (“cheat sheet”) to guide providers in delivering and documenting SBIR. Training of the clinical team members involves 1:1 or group in-person education and information sessions on how SBIR contributes to patient recovery and health (tailored to the specific patient populations/conditions served by each site), and how to complete and document SBIR using Connect Care. Technical assistance includes continuous engagement, by the research and implementation support team, with clinical team members and their leaders to build trust and to co-design the tailored support they need. Research staff are embedded in clinical sites to undertake the research activities of our project and to support clinical staff by offering regular coaching and troubleshooting concerning the delivery and documenting of SBIR. Quality improvement support involves continuous assessment of implementation, identifying “what worked’ or didn’t, and why, and provision of feedback reports on the clinical teams’ progress in implementing SBIR. We work proactively with clinical teams to refine the implementation strategies. The implementation sites and units were intentionally selected to ensure that no other major initiatives were occurring concurrently

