**Pre-implementation Phase (6 Months Control Period)**				

Baseline, for comparison of SBIR (Screening Brief Intervention, and Referral) effectiveness	Tobacco consumption, alcohol intake, and physical activity levels	Proportion of patients with tobacco consumption, alcohol misuse, and insufficient physical activity levels	Primary data collection from comparison patient group	Paper-based self-administered questionnaire

Pre-implementation (baseline) delivery of SBIR elements by clinical team members.	Providers’ baseline delivery of SBIR elements to patients	Proportion of patients being screened, advised, and referred for each risk factor	Connect Care documentation (electronic health records)	Connect Care data extraction, monthly time points for six months

Baseline	SBIR implementation readiness	Leadership engagement/support, resources for SBIR, providers’ motivation	Primary data collection from providers and organizational leaders	Self-administered questionnaire, interview, and observation

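### The coverage analysis reads Connect Care entries as delivered SBIR, although brief advice is known to be under-charted and the programme also trains staff to chart

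*Protocol article*

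**What the plan says.** The section 'Research plans for evaluating implementation outcomes and process' defines reach and coverage. The numbers of patients screened, advised and referred "in relation to each risk factor will be extracted each month from the Connect Care data". The coverage denominator is the "total number of patients seen by a participating unit in the same month". The effect of implementation is then read from a model: "A Poisson regression model will be used to estimate the difference between the post-intervention observed rate" and the spontaneous rate expected without SBIR. The model uses the six pre-implementation months and the last 12 of the 15 implementation months.

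Table 1 names the construct. The baseline row is headed "Pre-implementation (baseline) delivery of SBIR elements by clinical team members", its measure is "Proportion of patients being screened, advised, and referred for each risk factor", and its collection method is "Connect Care data extraction, monthly time points for six months". The matching row for the implementation phase again speaks of providers' delivery, reach and adherence, with Connect Care documentation as the only source.

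Two other sections bear on this. 'Expected Results and Applicability' reports, from experience to date: "When brief interventions are provided, they are often not documented in the Connect Care system". The same list says that screening is consistently done and documented. It also says that referral functions for alcohol and physical activity are not built into the system. 'Anticipated implementation challenges and strategies employed' lists staff training on "how to complete and document SBIR using Connect Care", an information sheet on delivering and documenting, coaching by embedded staff on both, and progress feedback.

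**The concern.** The outcome is named as delivery but measured as documentation. The article's own experience shows that the two differ for brief advice. The programme under evaluation also works on both at once: it asks staff to give more advice and teaches them to record it. A rise in charted advice can therefore come from more advice, from better charting of the same advice, or from both, and the Poisson contrast cannot tell these apart.

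The results are meant to inform spread across Alberta's hospitals. Decision-makers would want to know whether more patients were advised. As written, the plan would let a charting gain stand as a care gain, and would let absolute advice coverage be read as lower than it was.

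**Working it through.** No stated sample size, power or event figure depends on this point, so there is no figure of the plan to reproduce. What can be checked is how the stated estimand behaves.

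**Inputs**
- Numerator, denominator and comparison: as defined in the implementation-outcomes section.
- Same single source in both periods: Table 1.
- Charting of delivered advice is incomplete: 'Expected Results and Applicability', with no percentage.
- Charting completeness before (s0) and after (s1): not given. The values below are assumptions.
- True delivery before (d0) and after (d1): not given. Also assumed.
- No entries for care that was not given: assumed.

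**Formulas**
- Documented coverage = d × s
- Observed rate ratio = (d1 × s1)/(d0 × s0) = true ratio × (s1/s0)
- Observed difference = d1 × s1 − d0 × s0

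**Delivery unchanged (true ratio 1.00)**

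| s0 | s1 | Observed ratio s1/s0 |
|---|---|---|
| 0.5 | 0.5 | 1.00 |
| 0.5 | 0.7 | 1.40 |
| 0.3 | 0.5 | 1.67 |
| 0.5 | 0.9 | 1.80 |
| 0.3 | 0.7 | 2.33 |
| 0.7 | 0.5 | 0.71 |

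**Delivery rising from 10% to 20% (true ratio 2.00, true difference 10 points)**

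| s0 | s1 | Documented before | Documented after | Observed ratio | Observed difference |
|---|---|---|---|---|---|
| 0.5 | 0.5 | 0.10 × 0.5 = 5% | 0.20 × 0.5 = 10% | 2.00 | 5 points |
| 0.3 | 0.7 | 0.10 × 0.3 = 3% | 0.20 × 0.7 = 14% | 4.67 | 11 points |
| 0.7 | 0.5 | 0.10 × 0.7 = 7% | 0.20 × 0.5 = 10% | 1.43 | 3 points |

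**Reading the tables**
1. With equal completeness the ratio is preserved, but coverage and the difference shrink by the factor s; at s = 0.5 both are halved.
2. With unequal completeness the ratio is multiplied by s1/s0, in either direction.
3. Turned round, true ratio = observed ratio ÷ (s1/s0). An observed ratio of 2.00 would stand for 2.00/1.00 = 2.00, for 2.00/1.40 = 1.43, for 2.00 × 0.3/0.7 = 0.86, or for 2.00 × 0.7/0.5 = 2.80.

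**Does anything in the plan hold s1/s0 at 1?** Leaving out the first three implementation months is justified by the maturing quality of the intervention. It does not make charting in months 4 to 15 equal to charting before implementation. The provider conversations and the interviews during implementation are process evaluation; the article does not link them to the counts, and they give no completeness figure for either period.

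**The case against.** The best defence is that documentation is part of what the programme sets out to change. The article wants SBIR actions and their recording built into Connect Care workflows, and presents the electronic risk-factor record as a benefit in itself. Table 1 openly gives Connect Care documentation as the source. A rise in documented SBIR is then a real implementation result. This stands, and it is why relabelling is enough for the main outcome. It does not support calling the same count delivery or adherence.

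A second defence is that adherence is also explored with providers on a standard template, and that validation detail may sit in a fuller protocol or analysis plan. That is fair as to detail. The mismatch, however, lies in the stated outcome and its label, not in an omitted detail.

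A reader might infer stronger claims that the document does not support:
- *That the before-after ratio is inflated because baseline advice is rarely charted.* Nothing describes baseline charting. The report of poor charting is an observation from the project to date, given alongside early SBIR results, so it is no evidence of a large jump in completeness.
- *That documentation training begins only with implementation.* This is likely, since it belongs to the implementation strategies, but no start date is given.
- *That all three components are equally affected.* Screening is reported as consistently documented. For referral, the article reports unclear pathways and missing system functions, not uncharted referrals.
- *That enrolled controls show baseline delivery to be nil.* Those patients are recruited by research staff; the time series counts everyone seen by the unit, and the plan itself measures a baseline rate.

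**Conclusion.** The point holds for the advised component, less certainly for referral, and little for screening. If charting is incomplete but equal in both periods, absolute coverage and the rate difference are understated while the ratio is sound. If completeness differs between periods, the ratio is wrong by the factor s1/s0: 0.71 to 2.33 over the assumed pairs above. These figures illustrate a mechanism and are not estimates for this study. They assume no false entries. The true values, and so the size and net direction of the error, cannot be determined from the document. What can be said is that the planned contrast supports a conclusion about documented SBIR, and supports one about delivered SBIR only under an assumption of equal completeness that the article does not state and that its own training programme makes doubtful.

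**What to change.** 1. In the implementation-outcomes section and in both Table 1 rows, define the outcomes as documented screening, documented advice and documented referral.
2. State that the Poisson contrast with the spontaneous rate estimates a change in documented SBIR, and make no claim of increased delivery from the uncorrected ratio alone.
3. For advice and referral, pre-specify a sensitivity analysis that divides the observed ratio by a stated range of s1/s0, including values below and above 1, and report the value at which the apparent effect disappears. If absolute coverage or the difference is interpreted as delivery, state assumed levels of s0 and s1 as well, because the ratio alone does not correct them.

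A correction factor should not be taken from the 6-month calls. Enrolled controls are not offered the intervention and are screened on paper by research coordinators, so they cannot supply baseline completeness, and a question on being asked about risk factors would pick up study contact. Intervention participants are selected on having received brief intervention, so they do not represent all patients seen. Only about half of patients respond, and 1,000 of the 2,015 controls have already completed the call.

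The cost is a wording change and one extra analysis on data already planned. The headline claim becomes slightly narrower.
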